### Digital Health Care Technology

#### SH App and Samsung Galaxy Watch

The SH app, coupled with Samsung Galaxy Watch, can track a number of parameters, including (1) food and water intake (including calorie tracking), (2) sleep patterns, (3) blood oxygen saturation levels, (4) body composition, (5) body weight, (6) calorie intake, (7) heart rate, (8) blood pressure, and (9) habitual physical activity (step counts and minutes of moderate and physical activity completed per day).

The SH app uses biometrics obtained by the connected wearable device, the smartphone itself, and self-reporting to record variables such as accelerometry, heart rate, time, distance traveled, and speed. Data are then used for activity tracking by matching the signature characteristics of a wide range of exercises (such as walking, hiking, or swimming) to calculate step counts, the number of minutes of moderate and vigorous physical activity completed, and the number of calories expended. The SH app supports tracking of food intake during the day. For instance, users can record meals and snacks as well as fluid and caffeine intake. Macronutrients (proteins, carbohydrates, and fats) and micronutrients (vitamins and minerals) can be calculated. The SH app also implements sleep analysis, sleep duration tracking, and sleep stages to provide insights about the quantity and quality of sleep.

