### Recruitment Program

Participants will be identified from oncology services at Ysbyty Gwynedd Hospital, Betsi Cadwaladr University Health Board, by reviewing the outpatient clinic lists of each participating oncologist, advanced nurse practitioner, and clinical pharmacist on a daily basis. For potentially eligible patients, the appropriateness of proposing participation in this trial will be decided by the lead oncologist. At the end of the clinical consultation, if deemed appropriate, the clinician will introduce the study and provide the information leaflet, and a date in the future will be set for the volunteer to meet a member of the clinical research team to answer all the possible queries and to confirm sign-up for participation. If and when a participant agrees to proceed with the study, they will be asked to sign the consent form and will receive the smartwatch (and a smartphone, if required). The clinical research team member will help with the setup of the apps and smartwatch pairing and will provide a technical overview of both as well as the troubleshooting and contact information. Baseline questionnaires will be completed on a dedicated tablet or paper as per the recommended procedures with a standard approach to collect these patient-generated data with the supervision of the clinical research nurse or officer [16]. The same approach will be used to collect end-of-study questionnaires data. The expected recruitment period is January 2024 to June 2024, with the maximum duration of data collection for each participant set to up to 16 weeks. We anticipate being able to recruit about 5 patients per week over a 24-week period to reach our target.

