EQ-5D-5L: Participants’ HRQoL will be measured using the EQ-5D-5L questionnaire [20]. EQ-5D-5L is a widely used tool for assessing the domains of mobility, self-care, usual activities, pain or discomfort, and anxiety or depression as well as recording patients’ self-rated health on a visual analog scale.Multidimensional Fatigue Inventory Short Form: Multidimensional Fatigue Inventory Short Form [21] will be used to assess fatigue. This is a validated short form of the more in-depth Multidimensional Fatigue Inventory questionnaire [22] and uses 10 simple questions to assess physical, emotional, and cognitive fatigue [21].Satisfaction, Alertness, Timing, Efficiency and Duration (SATED): The SATED questionnaire [23] will be used to assess subjective sleep. SATED is a simple questionnaire to determine the degree of sleep fulfillment and to measure the dimensions of sleep health based on 5 simple questions [24]. It has been used in >150 peer-reviewed papers and studies.Patient Assessment of Chronic Illness Care: Patient Assessment of Chronic Illness Care questionnaire [25] will be used to assess experience with care. It is recommended for research and quality improvement and has been successfully deployed in digital oncology studies [26].Edmonton Symptom Assessment System (ESAS; digital form completed daily through the GK app): The global symptom burden will be assessed through ESAS [27]. ESAS has a recall time of 24 hours and is adapted to daily completion [28]. Daily total symptom distress scores (ESAS physical score+emotional score+well-being) [29] will be computed, and their temporal trajectories will be compared using general linear and random mixed effects models for longitudinal data [30].Global Physical Activity Questionnaire: Habitual physical activity will be assessed using the Global Physical Activity Questionnaire short form [31] and four unvalidated questions: (1) minutes of moderate physical activity completed per week, (2) minutes of vigorous physical activity completed per week, (3) number of sessions of strength training completed per week, and (4) number of sessions of balance training completed per week.Patient Activation Measure–13: Patient activation, an individual’s knowledge, skills, and confidence integral to managing their own health and health care, will be assessed using the Patient Activation Measure–13 [32].

Table 1 lists the timeline and type of data collected throughout the study period.

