Participants will then be presented with the mHealth solution: the GK app on a personal smartphone and a smartwatch paired with the SH app. The participant will be trained to use the apps and watch. The GK app features a set of interactive questionnaires to collect the baseline and periodic self-assessment data. Furthermore, the GK app provides timely reminders about the need to complete the self-assessments and data visualization analytics. Finally, the GK app collects and anonymizes data from the smartwatch and SH app for daily data collection on a dedicated remote server. The smartwatch adopted can be configured and used in different ways; each patient will be able to set up complementary apps offering extra functionalities such as the stress level analysis and to identify the preferred patterns of use. Overall, the data generated by the smartwatch will be collected and aggregated on a daily basis, including heart rate, sleep and physical activity patterns, and calories and food intake. The sampling of data will be dependent on the user settings and contingencies, such as charging at night or battery level. Throughout the 16-week study period, the smartwatch will continuously and unobtrusively record habitual physical activity, sleep patterns, energy expenditure, step counts, and oxygen saturation through its biosensors (Figure 1). For example, the amount of moderate and vigorous physical activity completed per week will be obtained automatically through the study using heart rate data recorded by the wearable smartwatch. Specifically, the maximal heart rate will first be predicted using the following formula: maximal heart rate = 207 − (0.7 × age) [33].

**Table 1 table1:** Data collected at each time point of the study.

	Baseline: day 0	Day 1-14	Daily from baseline	Thrice weekly (alternate days)	Weekly	End of the study (4 months +7 or −7 days)
Eligibility	✓					
Informed consent	✓					
Demographics	✓					
Height, weight, BMI, and waist circumference	✓^a^					✓
WHO^b^ performance status	✓					
Medical history or concomitant conditions and medications	✓					✓
Cancer type and stage	✓					
ED-5D-5L	✓^a^					✓
MFI^c^-10	✓^a^					✓
SATED^d^	✓^a^					✓
PACIC^e^	✓^a^					✓
PAM 13^f^	✓^a^					
Issue of smartwatch and Android device if required	✓^a^					
Food diary				✓		
Weight					✓	
Physical activity appointment including cardio-respiratory fitness and muscular strength		✓				
GPAQ^g^		✓				✓
Habitual physical activity assessment		✓				

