Minutes of activity done by patient including strength and balance					✓	
Borg’s CR100 rating of perceived exertion scale					✓	
ESAS^h^			✓			✓
Continuous smartwatch data collection	✓^i^	✓	✓			
Usability questionnaire						✓
Adverse event assessment	✓^i^	✓	✓	✓	✓	✓
Collection of UKONS^j^	✓^i^	✓	✓	✓	✓	✓

^a^Conducted in person at baseline assessment visit.

^b^WHO: World Health Organization.

^c^MFI-10: Multidimensional Fatigue Inventory Short Form.

^d^SATED: Satisfaction, Alertness, Timing, Efficiency and Duration.

^e^PACIC: Patient Assessment of Chronic Illness Care.

^f^PAM-13: Patient Activation Measure–13.

^g^GPAQ: Global Physical Activity Questionnaire.

^h^ESAS: Edmonton Symptom Assessment System.

^i^To be collected from informed consent onward.

^j^UKONS: United Kingdom Oncology Nursing Society.

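### The first GPAQ is taken 1 to 14 days after the watch and apps are issued, so the GPAQ change has no pre-device starting value (low priority, cheap to improve)

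*Protocol article*

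**What the plan says.** Study Procedures, Table 1: the row "Issue of smartwatch and Android device if required" is ticked under day 0 and marked as done in person. The row "Continuous smartwatch data collection" carries a footnote that starts it at informed consent.

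Recruitment Program: once a participant agrees, "they will be asked to sign the consent form and will receive the smartwatch (and a smartphone, if required", and at the same contact "The clinical research team member will help with the setup of the apps and smartwatch pairing".

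On activity, Study Procedures states: "Habitual physical activity will be assessed using the Global Physical Activity Questionnaire short form", together with four unvalidated questions. In Table 1 the GPAQ has two ticks, days 1-14 and end of study. The fitness and strength appointment and the habitual activity assessment are also at days 1-14. The row "Minutes of activity done by patient including strength and balance" is weekly. No self-reported activity measure is ticked on day 0.

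Four other questionnaires have a start and an end value in Table 1: EQ-5D-5L, MFI-10, SATED and PACIC. All four start on day 0. PAM-13 is also done on day 0, without an end value.

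Secondary Outcomes makes every measure in Study Procedures a secondary outcome, collected to learn which way and how far it moves, in preparation for later trials.

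**The concern.** The devices are not neutral with respect to activity. The section on the SH app and watch lists, among the parameters tracked, "habitual physical activity (step counts and minutes of moderate and physical activity completed per day". The GK App section adds that patients view displays of their data. A participant who answers the first GPAQ at day 10, say, has had this feedback for ten days.

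If tracking changes activity early, part of that change is already in the starting value, and the start-to-end difference leaves it out. The weekly questions and the watch record can show activity moving after issue, but they also begin after issue and cannot supply the missing earlier level. Device exposure before the first GPAQ also differs between participants. At stake is how one exploratory change score can be read when later trials are planned.

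**Working it through.** **Schedule, side by side (Table 1)**

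| Measure | First value | Last value |
|---|---|---|
| Watch and phone issue | day 0 | n/a |
| EQ-5D-5L, MFI-10, SATED, PACIC | day 0 | end of study |
| GPAQ | days 1-14 | end of study |
| Self-reported activity minutes | weekly, after issue | n/a |

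No other section gives a GPAQ date that overrides the table.

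**What the timing does to the change score.** Let A be a participant's GPAQ level before the device, r(d) the shift in that level after d days with the device, and c the shift by end of study.

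- Change as planned: (A + c) − (A + r(d)) = c − r(d), with d between 1 and 14.
- Change from a pre-device day 0 value: (A + c) − A = c.
- Difference between the two: r(d).

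If r(d) = 0, the schedule costs nothing. If activity rises early and stays up, the planned change understates c. The document gives no value for r(d), so neither its size nor its sign can be calculated.

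**Elapsed time.** These figures describe the schedule and do not measure bias.

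- Follow-up is 16 weeks × 7 = 112 days. Device time before the first GPAQ is 1/112 = 0.9% to 14/112 = 12.5% of it.
- The last column is headed "End of the study (4 months +7 or −7 days". Taking the end as day 112, the window is day 105 to day 119.
- GPAQ to GPAQ: shortest 105 − 14 = 91 days, longest 119 − 1 = 118 days, spread 27 days.
- From day 0: 105 to 119 days, spread 14 days.
- Reading the end as four calendar months (120 to 123 days), the shares are 1/123 = 0.8% to 14/120 = 11.7%. For any one end day the spreads stay at 27 and 14 days.

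**Plan's own figure.** Statistical Considerations gives a confidence interval of plus or minus 10% for 50% engagement with 100 participants: 1.96 × √(0.5 × 0.5 / 100) = 0.098. It reproduces, and GPAQ timing does not enter it.

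**The case against.** The strongest reply is that nobody needs a pre-device activity value here. Study Goals and Expected Findings sorts the secondary end points: the clinical impact of the solution is to be judged on symptom burden, quality of life and perceived care, while physical activity sits with diet and sleep under patterns over time. The quality-of-life and perceived-care questionnaires are on day 0, which broadly fits that division. This stands and lowers the weight of the point. It does not remove it, because Secondary Outcomes asks for the sign and size of change in every secondary measure, the GPAQ included.

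The early response is also assumed. The protocol describes the watch as unobtrusive, and the coaching it describes concerns sleep. The GPAQ is presented as a measure of habitual activity with no recall period given, so an answer on day 1 or 2 may mostly describe life before the device. That is less secure by day 14, but it means the effect could be near zero.

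The days 1-14 placement is coherent, since it keeps the GPAQ with the rest of the activity work-up. No reason is given that would require this.

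The order of events within day 0 is not fixed. Recruitment Program mentions hand-over and setup before the baseline questionnaires, whereas Study Procedures introduces the devices after listing them. Neither moves the GPAQ to day 0.

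A reader might infer that up to 12.5% of any activity effect is lost, or that the 27-day spread is a measure of error. The document supports neither: these are elapsed times, and nothing in it ties the GPAQ score to interval length.

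**Conclusion.** The point holds as a low-priority improvement. As scheduled, the GPAQ change runs from an early on-device value to an end-of-study value, and no self-reported activity measure precedes device issue. This rests on Table 1 as printed and on device hand-over at the consent contact. Any bias in the change equals the early response r(d), which cannot be derived and may be small.

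Two stronger readings should be resisted. One is that the schedule undermines the study's conclusions: the primary outcome is feasibility, and neither it nor the sample size uses the GPAQ. The other is that a day 0 GPAQ would yield the device's effect on activity: with no control group, the change could not be attributed to the device in either case. Nor is there a contradiction in the document; Table 1 is clear, and the point challenges a choice it makes.

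**What to change.** Move the first GPAQ tick in Table 1 from days 1-14 to day 0, and add a clause that it is completed in person before the watch and apps are set up. Web Portals and Tablets puts activity and patient activation on the same survey platform, and PAM-13 is already done in person that day, so no new visit or system is needed.

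Leave the fitness and strength appointment at days 1-14. Leave the four activity questions on their weekly schedule: the watch prompts them, so a day 0 entry before setup would need a separate arrangement.

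The cost is a few more minutes at a visit that already holds consent, body measurements, five questionnaires, device issue and training. The GPAQ would also no longer sit with the rest of the activity work-up.

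If the GPAQ has to stay at days 1-14, record the days since device issue for each participant and report the change as measured from an early on-device value.

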**Figure 1 figure1:**
[figure not shown]
Study schematic of the trial design (longitudinal and observational) with features of the patient-generated data collected through the smartwatch (objective and mostly continuous) and app (subjective and repeated measures or snapshots).

If a patient obtains a higher than predicted maximal heart rate during exercise, the actual maximal heart rate will replace the predicted maximal heart rate. The resting heart rate will then be recorded automatically by the watch. Heart rate zones will then be used to identify habitual physical activity intensity: very light (<30% heart rate reserve [HRR]), light (30%-39% HRR), moderate (40%-59% HRR), vigorous (60%-89% HRR), and near maximal to maximal (≥90% HRR) [34].

Energy expenditure during structured exercise will be estimated from the power output calculated from the mode of exercise, distance completed, and floors climbed. Other measurements such as body fat percentage, oxygen saturation, and blood pressure will be obtained using the standard features available within the smartwatch and smartphone.

The smartwatch will also prompt the participant to complete the ESAS questionnaire on a daily basis and to self-report the amount of habitual physical activity using the 4 abovementioned unvalidated questions on a weekly basis.

The SH app uses the Samsung Galaxy Watch to monitor sleep patterns, track sleep movements, and generate a sleep score. Additionally, the SH app provides daily goals and coaching programs based on sleep data to help improve sleep habits. Sleep analysis uses Samsung proprietary algorithms currently available through the public release of the SH app.

The SH app also allows the self-logging of the type and timing of meals and snacks. It is possible to set a daily target for caloric intake. After inputting details of the food type and quantity from a menu of common meals, the SH app provides a real-time view of the current calorie count for the day and a summary of the nutritional intake to determine if one is within the recommended levels. Moreover, it provides access to an overall dietary report over the span of a week.

### Contact From the Research Team

To ensure compliance with the trial, a telephone call by a member of the research team to all participants will be arranged at week 1 and then, if required, every 4 weeks until the end of the trial data collection period. The nature of these calls is to resolve any problems or concerns. The frequency of calls will be arranged and adapted by the research team members on an individual basis according to each participant’s needs and wishes. On the basis of prior experience with digital monitoring in patients with cancer [19], we believe that offering a regular opportunity to speak to someone who can help reassures participants, reduces anxiety, and in turn facilitates more accurate and consistent data collection.

### Concomitant Care Permitted During the Trial

During the study period, each participant will receive the indicated surveillance and routine care in accordance with their needs and clinical condition. Thus, any form of intervention for the underlying cancer or any intercurrent issue will be allowed (and recorded). Similarly, any type of diagnostic investigation, workup, or health care provider encounter will be permitted. To maximize participants’ safety, multiple measures have been put into place.

We will provide technical support and contact information for any inquiries, along with an escalation plan for clinical needs. This support includes online assistance, drop-in clinics, and remote technical support during office hours. Patients will be directed for any medical concerns to contact the Acute Oncology Hotline: 24/7 availability of the Acute Oncology Hotline support, to which participants have been accustomed during the on-treatment period in Alaw (oncology department in Ysbyty Gwynedd, Bangor, United Kingdom). The occurrence of any unplanned health care encounter (with general practitioner, district nurse, practitioner nurse, specialist nurse, dietician, physiotherapist, psychologist, occupational therapist, clinical pharmacist, or any hospital specialist) will be recorded with a weekly question through the GK app. Finally, members of the research team will be given access to a web-based portal, where they can log in and access patient data. Although data will not be checked with regard to patient clinical condition (the portal is designed to check only if data have been collected or not), for safety reasons, if when checking for data availability, the research team will notice any symptom with a severity score of ≥7 (on a 10-point scale) or any other potentially serious medical issue, the lead clinician or the consultant oncologist of the week (available 24/7) will be informed, and they will decide accordingly whether it is sensible to contact the participant to inquire about their complaint and select the most appropriate action.

### Primary Outcome

The main outcome of this trial is to assess the feasibility of mHealth monitoring in survivors of cancer not receiving toxic anticancer treatment. A priori criteria based on a traffic light system will be used to determine whether mHealth monitoring is unfeasible and future trials should be halted (red), whether changes to the study design or mHealth intervention are required before future trials are initiated (amber), or whether mHealth monitoring is considered feasible, and progress to future trials can occur without modification of the study design or intervention (green) [35]. The traffic light system will be applied at the end of the 16-week study period following collection of the last follow-up assessment from the last participant (on an intention-to-treat basis) to the following feasibility outcomes: eligibility (no set criteria but number of patients screened and eligible will be recorded); recruitment rate (green: n =>75, amber: n =≥50, and red: n=<50); acceptability of randomization and assessment procedure (no set criteria but the characteristics [and the proportion by group] of participants withdrawing post randomization will be captured); mHealth acceptability (green: ≥50/100, ≥50% of participants engage with the app at least once a week on at least 12 weeks out of the 16-week study, amber: ≥50/100, ≥50% of participants engage with the app at least once a week on at least 8 weeks out of the 16-week study, and red: <50/100, <50% of participants engage with the GK app at least once a week on at least 8 weeks out of the 16-week study); attrition rate (green: 20/100, <20% dropout rate, amber: ≤40/100, ≤40% dropout rate, and red: <40/100, >40% dropout rate); and missing data (green: <20/100, <20% of data missing, amber: ≤40/100, ≤40% of data missing, and red: >40/100, >40% of data missing). Engagement with the GK app is defined as logging on and completing at least 1 of the scheduled measures (ESAS, food intake, or habitual physical activity).

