### Statistical Considerations

The study’s primary outcome is feasibility, which, by design, is assessed by multiple outcomes (as described above). Arguably, the most important of these is patient engagement with the mHealth solution, and we have defined the solution as feasible if at least 50% (50/100) of the participants engage with the app at least once a week in 8 of the 16 study weeks. If we recruit 100 eligible participants, we will be able to estimate an engagement rate of 50% (n=50) with a 95% CI of +10% or −10%, whereby the width of the CI (in percentage) was calculated as follows:

1.96×√(p×(1−p)/n) **(1)**

where p is the percentage (50%) and n is the intended sample size (100). For this feasibility study, we considered this CI appropriate for estimating drop-off rates in future studies. Finally, we considered this sample size suitable for the preplanned exploratory subgroup analyses.

The main analysis of the primary outcome (compliance) will be performed on an intention-to-treat basis. Similarly, the secondary outcomes will be evaluated on an intention-to-treat basis. However, for the secondary outcomes, preplanned subgroup and sensitivity analyses will also be conducted. They will include (1) subgroups with at least 75% (75/100) of available patient-generated data (from the app and the smartwatch combined) to exclude unengaged participants and focus on the most committed participants, (2) subgroups defined by the performance status and presence or absence of evidence of neoplastic disease, and (3) subgroups defined by sex and median age. For the primary outcome, no form of inference will be performed on the missing data, as they provide the main outcome of the study. For secondary analyses, neither mean imputation nor the last observation carried forward will be used [50]. However, based on the proportion of missing data, exploratory analyses including low-rank approximation–based imputation [51] could be performed to ensure that the observed effect sizes remain of the same order of magnitude with this approach as well.

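### The engagement level that Statistical Considerations calls feasible is the level that the traffic light grades amber, and no rule says how the four lights combine

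*Protocol article*

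**What the plan says.** Primary Outcome sets up one three-way verdict. The "traffic light system will be used to determine whether mHealth monitoring is unfeasible and future trials should be halted (red"). The second colour decides "whether changes to the study design or mHealth intervention are required before future trials are initiated (amber"), and the third decides "whether mHealth monitoring is considered feasible, and progress to future trials can occur without modification of the study design or intervention (green"). Of the three, only green is described as feasible.

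Four outcomes have cut-offs:
- Recruitment: "recruitment rate (green: n =>75, amber: n =≥50, and red: n=<50").
- mHealth acceptability, which is app engagement: "amber: ≥50/100, ≥50% of participants engage with the app at least once a week on at least 8 weeks out of the 16-week study". Green needs the same share of participants in at least 12 weeks. Red is a share below 50% at the 8-week level.
- Attrition: "attrition rate (green: 20/100, <20% dropout rate, amber: ≤40/100, ≤40% dropout rate, and red: <40/100, >40% dropout rate").
- Missing data: "missing data (green: <20/100, <20% of data missing, amber: ≤40/100, ≤40% of data missing, and red: >40/100, >40% of data missing").

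Two further outcomes, eligibility and acceptability of randomization and assessment, are listed without cut-offs. The section does not say what the overall verdict is when the four graded outcomes show different colours.

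Statistical Considerations notes that feasibility is assessed by several outcomes and ranks engagement as arguably the most important. It then states: "we have defined the solution as feasible if at least 50% (50/100) of the participants engage with the app at least once a week", and the sentence goes on to set the level at 8 of the 16 weeks. The Abstract (Results) and the Objectives use the same engagement criterion, with no other component, to spell out the hypothesis that mHealth monitoring will be feasible.

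**The concern.** The verdict on feasibility is the trial's primary conclusion, and the next step depends on it. The Discussion says that efficacy studies follow if the solution is feasible, and Strengths and Limitations foresees a randomized study if feasibility is shown. The article prints two thresholds for that conclusion. One accepts 50% of participants at 8 weeks; the other treats that level as a reason to alter the design or the intervention first.

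The criteria are presented as set in advance. If two definitions stand, the choice between them can be made after the engagement figures are known. The same freedom exists when engagement passes and another graded outcome is red, because nothing printed says which one governs.

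**Working it through.** **The plan's own figure.** Inputs from Statistical Considerations: p = 0.50, n = 100. The half-width is 1.96 × √(0.5 × 0.5 / 100) = 1.96 × 0.05 = 0.098, or 9.8 points. This reproduces the stated 10 points. The calculation is sound and is not part of the problem. It applies equally to a 50% rate measured at 8 or at 12 weeks, so it does not settle which level means feasible.

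**The two engagement rules side by side.** Let E8 be the share of participants who engage in at least 8 of the 16 weeks, and E12 the share who do so in at least 12. Anyone counted in E12 is also counted in E8, so E12 ≤ E8 and three cases cover everything:

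| Result | Statistical Considerations, Abstract, Objectives | Engagement light in Primary Outcome |
|---|---|---|
| E8 < 50% | not feasible | red |
| E8 ≥ 50% and E12 < 50% | feasible | amber: changes first |
| E12 ≥ 50% | feasible | green: feasible unmodified |

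The rules agree in the first and third rows and disagree throughout the second. That row is the whole amber band for engagement. No rule for combining outcomes is needed to see this.

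**Engagement passes while another light is red.** Suppose 100 enrol, all engage weekly through week 8, 45 then drop out, and 55 finish and stay engaged.
- Recruitment: 100, green.
- Engagement: E8 = 100/100 = 100% and E12 is at least 55/100 = 55%. This is green, and feasible under Statistical Considerations.
- Attrition: 45/100 = 45%, above 40%, red on the printed percentage. The count printed beside it has the inequality reversed, so I use the percentage.
- Missing data: if every entry is complete until dropout and the schedule is even over time, 45 × 0.5 / 100 = 22.5%, amber.

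The four lights are green, green, red and amber. The article gives no way to turn them into one verdict.

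**Recruitment as an example.** With 45 enrolled and 30 engaged, the percentage is 30/45 = 67%, which meets the 50% rule. The count is 30 against the printed 50/100, which does not. This case is ambiguous, so I do not rely on it.

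**The case against.** Several counterarguments carry weight.

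*One red does not mean halt.* A reader might infer that a single result can be both feasible and grounds to halt future trials. That needs a rule under which any red, or the worst light, decides. Primary Outcome says the lights will be used to reach the verdict; it never says that one red among four stops future work. This objection stands, and the stronger reading should not be claimed.

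*Statistical Considerations keeps the several outcomes in force.* It names engagement as the leading one, and it speaks of the solution rather than the study. An app can do well on engagement while trial processes fall short. This softens the reading that engagement is the sole verdict. It does not remove the contradiction, because the engagement component alone has two thresholds. The Abstract and Objectives also attach the 8-week level to mHealth monitoring, which is what the traffic light judges.

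*A combination rule may sit in a fuller protocol or analysis plan.* It may, and its absence from an article would not be a finding on its own. An undisclosed rule would still leave the printed 8-week and 12-week definitions in conflict.

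*Counting colour combinations overstates the size.* Four lights give 3^4 = 81 combinations. Of the 54 with engagement amber or green, 38 contain at least one red among the other three. These counts are correct but are not likelihoods: the combinations are not equally probable, and dropout drives both missing data and engagement.

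*A worst-light rule is not the obvious remedy.* Under it, recruitment below 50 would by itself give a red verdict, while the Contingency Plans section accepts the risk of slow recruitment. The choice of rule belongs to the sponsor.

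**Conclusion.** The concern holds in this form. The article calls feasible, in three places, an engagement level that Primary Outcome grades amber. The conflict covers every result with at least 50% of participants engaged at 8 weeks and fewer than 50% at 12 weeks, and on the engagement component it covers nothing else. How likely such a result is cannot be derived from the documents.

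The lack of a printed rule for mixed colours is a second, lesser part of the point. It matters because an engagement-only definition stands beside four graded outcomes, and the 45% attrition example shows that they can diverge. It does not show that the plan orders a halt.

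Two reading assumptions are used: 8 of the 16 weeks means at least 8, and attrition is red above 40%, as the percentage states.

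**What to change.** 1. Reword the Abstract (Results), Objectives and Statistical Considerations so that 50% of participants in at least 8 weeks is the amber level of the engagement component, and feasible without modification requires the 12-week green level.
2. State, before data are seen, one rule for how the four graded lights give the overall verdict. The sponsor should choose it, for example by saying whether engagement leads or whether any red blocks a feasible verdict.
3. Report all four lights whatever the verdict. If data have already been seen, disclose when the rule was set.
4. In the same edit, make the attrition red count agree with its percentage.

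The cost is a few sentences. The sample size and its precision calculation are unchanged. The downside is a somewhat less favourable label for a study that reaches 50% engagement at 8 weeks but not at 12.
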